## Abstract

**Background:**

Neo-adjuvant chemotherapy followed by radical cystectomy with extended pelvic lymph node dissection is considered to be the treatment of choice for patients with muscle invasive bladder cancer (MIBC). Despite this aggressive treatment the outcome is poor and ultimately, 30% of the patients with ≥pT3 tumors develop a pelvic recurrence. We hypothesize that postoperative adjuvant external beam radiotherapy (EBRT) might prevent local and lymph node recurrence and improve disease free- and overall survival as loco-regional recurrence is linked to the development of distant metastasis.

**Methods:**

We plan to perform a multicentric prospective phase two study including 76 patients. Eligible patients are patients with MIBC, treated with radical cystectomy and presenting with ≥1 of the following characteristics:Pathological (p)T3 stage + presence of lymphovascular invasion on pathological examinationpT4 stage<10 lymph nodes removedpositive lymph nodespositive surgical margins

Patients will have a ^18^F–FDG PET-CT to rule out the presence of distant metastasis prior to EBRT. A median dose of 50 Gy in 25 fractions is prescribed to the pelvic lymph node regions with inclusion of the operative bladder bed in case of a positive surgical margin. Patients with suspected lymph nodes on PET- CT can still be included in the trial, but a simultaneous integrated boost to 74Gy to the positive lymph nodes will be delivered. Blood and urine samples will be collected on day-1 and last day of EBRT for evaluation of biomarkers. The primary endpoint is evaluation of acute ≥Grade 3 intestinal or grade 4 urinary toxicity, in case of a neo-bladder reconstruction, within 12 weeks after EBRT. Secondary endpoints are: assessment of QOL, late RTOG toxicity, local control, disease free survival and overall survival. Biomarkers in urine and blood will be correlated with secondary survival endpoints.

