### Objectives

*Primary endpoint*
○ Acute toxicity defined as toxicity occurring during or within 3 months following adjuvant EBRT and scored by:▪ Acute Radiation Therapy Oncology Group (RTOG) small and large intestine toxicity [28] and Common toxicity criteria version 4.0 (CTC v4.0) [29]▪ Acute RTOG [28] and CTC v4.0 [29] bladder toxicity for patients with a neobladder only

*Secondary endpoints*
○ Quality of life (QOL) scoring using the EORTC QLQ-C30 supplemented with QLQ-BLM30 prior to, at the end and 1 month after adjuvant EBRT, then 3-monthly during the first year and 6-monthly up to 2 years.○ Assessment of quality-adjusted-life-years with the EuroQol classification system (EQ-5D) [30]. A written consent to use this system was obtained from the EuroQol Group Foundation.○ Assessment of erectile function using the International Index of Erectile Function (IIEF) questionnaire [31] in males and sexual function in females [32].○ Assessment of voiding pattern using the International prostate Symptom Score (I-PSS) [33] and International Consultation on Incontinence Modular Questionnaire Urinary Incontinence (ICIQ-UI) Short Form [34] for patients with a neobladder.○ Late toxicity due to radiotherapy will be scored using RTOG [28] and CTC v4.0 [29] scoring systems. Late toxicity is defined as toxicity lasting more than 3 months after cessation of adjuvant EBRT, or starting more than 3 months after the end of adjuvant radiotherapy.○ Local control rate defined as absence of recurrence within the pelvis. This will be evaluated on pelvic CT scans performed on predefined time-points (see below) or in case of suspicion of recurrence.○ DFS defined as survival without evidence of disease recurrence (neither local recurrence, recurrence in lymph nodes or distant metastasis) and is calculated from date of radical cystectomy till diagnosis of local, regional or distant recurrence on CT scan at predefined time-points or in case of suspicion of recurrence.○ Bladder cancer specific survival calculated from date of radical cystectomy till death due to MIBC.○ Overall survival calculated from date of radical cystectomy till death of any cause.○ Serum samples and urine samples after cystectomy will be collected and stored in a biobank. Biomarkers will be evaluated on all samples in duplicate and correlated with DFS and bladder cancer specific survival.

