### Statistical analysis

#### Sample size

We plan to perform a multicentric prospective phase 2 study in which 76 patients will be enrolled. With this sample size there is 95% likelihood that no more than 25% ± 10% [21] of the patients will develop severe toxicity (i.e. grade ≥ 3 toxicity requiring hospitalization and/or surgical re-intervention) after adjuvant radiotherapy. This number takes into account 5% percentage of missing data.

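### Whether a severe acute urinary event counts towards the primary endpoint depends on the section read, and a pooled rate could mask urinary toxicity in neobladder patients

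*Protocol article*

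**What the plan says.** Four places in the protocol article describe the primary toxicity outcome.

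- **Abstract, Methods:** a single event, "acute ≥Grade 3 intestinal or grade 4 urinary toxicity, in case of a neo-bladder reconstruction, within 12 weeks after EBRT".
- **Objectives, primary endpoint:** two separate items. Intestinal toxicity (RTOG and CTC v4.0) has no restriction on patients. The second item is "bladder toxicity for patients with a neobladder only". Neither has a grade threshold, and no rule for combining them is given.
- **Statistical analysis, Sample size:** "no more than 25% ± 10% [21] of the patients will develop severe toxicity", where severe means "grade ≥ 3 toxicity requiring hospitalization and/or surgical re-intervention". Organ and diversion are not mentioned. On this basis "76 patients will be enrolled", and "This number takes into account 5% percentage of missing data".
- **Data analysis:** toxicity of any kind from the start of radiotherapy until 3 months after it, with no limit by organ, grade or diversion.

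Eligibility requires a radical cystectomy but does not mention the type of urinary diversion. The article gives no expected neobladder share, no expected urinary toxicity rate and no explicit denominator for the urinary component. The Background cites reference [21], the source attached to the 25%, as one of two reports of severe intestinal toxicity.

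**The concern.** Every patient can have an intestinal event. Under the abstract and the Objectives, only neobladder patients can have an acute urinary one. Two problems follow.

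- **Classification.** A severe acute urinary event in a patient with another diversion is outside the primary endpoint in two sections and inside it in the other two. The reported rate would then depend on which section the analyst follows.
- **Masking.** If the two components are pooled and divided by all patients, the result depends on case mix as well as on toxicity. An unfavourable urinary rate in a small neobladder group could disappear within the precision that the plan allows itself.

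The Discussion states the aim as supporting the view that toxicity with modern radiotherapy is acceptable. Both problems bear directly on that conclusion.

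**Working it through.** **1. The plan's own figure.** Inputs from the Sample size section: expected rate 25%, margin 10 points, 95% confidence, 5% missing. For a single proportion, n = 1.96² × 0.25 × 0.75 / 0.10² = 72.03, and 72.03 / 0.95 = 75.8, so 76. The figure reproduces. The half-width with 72 evaluable patients is 10.0 points. It is sized on one rate over all patients.

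**2. The same event under the four passages.** Each event is assumed to be acute and to lead to hospitalization.

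| Event | Abstract | Objectives | Sample size | Data analysis |
|---|---|---|---|---|
| Grade ≥3 intestinal | counts | scored, no threshold | counts | counts |
| Grade 4 urinary, neobladder | counts | scored, no threshold | counts | counts |
| Grade 3 urinary, neobladder | does not count | scored, no threshold | counts | counts |
| Grade ≥3 urinary, other diversion | does not count | not scored | counts | counts |

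The last two rows are the contradiction.

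**3. How many events could turn on it.** Assume neobladder shares of 10%, 20% and 30% of 72 evaluable patients (7, 14 and 22 patients), leaving 65, 58 and 50 with another diversion. If 10% of these had a severe acute urinary event (also an assumption), that is 6.5, 5.8 and 5.0 events. Divided by 72, this is 9.0, 8.1 and 6.9 points of the all-patient rate, counted or not according to the section.

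**4. Masking if the components are pooled.** The most that the urinary component can add, with no overlap with intestinal events, is (neobladder patients / 72) × urinary rate. At an assumed urinary rate of 20%:

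- 10% share: 7/72 × 0.20 = 1.9 points
- 20% share: 14/72 × 0.20 = 3.9 points
- 30% share: 22/72 × 0.20 = 6.1 points
- 50% share: 36/72 × 0.20 = 10.0 points

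The first three lie inside the plan's ±10 points; the last equals it. As an example, 3 events in 14 neobladder patients is 21% (exact 95% CI 4.7–50.8%), but appears as 3/72 = 4% of all patients.

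The masking is stronger if intestinal toxicity proves lower than 25%. Assume an intestinal rate of 10% and independence, so that the pooled rate is 0.10 + share × urinary rate × 0.90. It stays at or below 25% as long as the urinary rate does not exceed 0.15 / (0.90 × share). That limit is 83%, 56% and 33% at shares of 20%, 30% and 50%.

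**5. What a separate urinary rate could show.** With no urinary events among m neobladder patients, the one-sided 95% upper bound is 1 − 0.05^(1/m): 35% for m = 7, 19% for m = 14 and 13% for m = 22. The estimate would be imprecise, and the pooled figure hides that imprecision.

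**The case against.** Several counter-arguments carry weight.

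- **A reader might infer that severe urinary toxicity with another diversion is never counted.** The documents do not support this. The Sample size definition would count such an event if it led to hospitalization or surgery, the Data analysis definition would count it regardless, and late toxicity has no neobladder limit. It is uncounted only under the abstract and the Objectives.
- **A reader might infer that the urinary component is certain to be diluted over all patients.** This is an inference from the abstract's composite taken together with the single all-patient target. The Objectives list the urinary item separately with its own population, and no passage rules out separate reporting. Nor does any passage provide for it or state the denominator.
- **A reader might infer that a high urinary rate would barely move the result.** This holds only for small neobladder shares. At a 30% urinary rate with no overlap, the addition is 0.30 × 0.30 = 9 points at a 30% share and 0.50 × 0.30 = 15 points at 50%.
- **Limiting a bladder scale to patients with a reconstructed bladder is sensible**, since every patient has had a cystectomy. This stands. It does not explain leaving all other acute urinary-tract toxicity out of the endpoint when CTC v4.0 is already in use.
- **Component tables and exact intervals commonly belong in the analysis plan.** This also stands, and their absence alone would be no finding. What counts as an event, and in whom, is fixed in this document, and it is fixed in conflicting ways.

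**Conclusion.** The point holds in a limited form. The contradiction is textual and needs no assumption: the abstract and Objectives restrict acute urinary events to neobladder patients, the Sample size and Data analysis sections do not, and the urinary grade threshold differs as well. The masking is conditional on the abstract's composite being analysed against the all-patient target. Its size, at most 1.9–6.1 points, rests on assumed neobladder shares of 10–30% and an assumed urinary rate of 20%, since the protocol gives neither figure; it weakens as the share grows. The sample size calculation itself is correct. The matter should be settled before analysis, because it affects what the trial can say about acceptable toxicity in either diversion group.

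**What to change.** - Reconcile the abstract, Objectives, Sample size and Data analysis to one definition of the primary endpoint, including the urinary grade threshold and the denominator of each component.
- State that the 25% ± 10 point precision target applies to the intestinal rate over all patients. This agrees with the Background's use of reference [21] for severe intestinal toxicity.
- Report the urinary rate separately, with neobladder patients as the denominator and an exact confidence interval.
- Record acute CTC v4.0 urinary-tract toxicity in all patients and report it by diversion type. Keep the RTOG bladder scale for neobladder patients.

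The cost is revised endpoint wording, one extra table and some added CTC scoring in patients without a neobladder. The neobladder interval will be wide and should be shown as such. The sample size stays at 76.

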**Discussion:**

This is a prospective phase 2 trial re-assessing the feasibility of adjuvant radiotherapy in high-risk MIBC.

**Trial registration:**

The Ethics committee of the Ghent University Hospital (EC2014/0630) approved this study on 31/07/2014.

Trial registration on Clinicaltrials.gov (NCT02397434) on November 19, 2014.

## Background

Muscle invasive bladder cancer (MIBC) is the ninth most frequently diagnosed cancer and ranks 13th in terms of causes of death worldwide [1]. The incidence of bladder cancer increases steadily with age. Due to improved life expectancy, the number of patients diagnosed with MIBC is expected to increase in the future.

A radical cystectomy combined with an extended pelvic lymph node dissection (ePLND) is considered to be the treatment of choice. Cisplatin-based neo-adjuvant chemotherapy improves survival outcomes and is recommended for patients with cT2-T4a N0–1 M0 MIBC [2, 3]. Despite this multimodality treatment the outcome did not altered significantly over the last 30 years [4] and remains poor with 5-years overall survival rates ranging between 50 [5] and 60% [6] to 65% [7]. For patients with ≥pT3 MIBC the 5-year overall survival even drops to as low as 22% [8]. Others have reported somewhat better results with a 5-year bladder cancer specific survival of 31 and 48% for T4 and T3 MIBC patients respectively [6].

Besides the high rate of systemic recurrences, loco-regional control is equally important. Approximately 30% of patients with ≥pT3 tumors develop a pelvic recurrence [8–10]. For instance, in a contemporary monocentric analysis from a high-volume, tertiary center focusing on 334 pT3–4 pN0–1 MIBC patients, 31% of patients developed a pelvic recurrence, 34% of which had loco-regional only failure. Chemotherapy, whether immediately postoperative (adjuvant) or delayed at time of recurrence, might improve the outcome of patients with MIBC as was suggested in a recent meta-analysis [11]. Unfortunately, these results are based on very inhomogeneous data. The conclusions of this meta-analysis are not considered to be robust and it remains unclear which patients really benefit from it [12]. Generally, neo-adjuvant chemotherapy is preferred, which does not interfere with this trial. Currently, there are also several trials already running or being initiated looking at the use of adjuvant immunotherapy with MIBC. While this approach looks promising, eventual adjuvant immunotherapy does not exclude adjuvant radiotherapy. In fact, there might be an additional benefit in the combination [13].

The rationale for adjuvant radiotherapy also reflects that attempts to salvage patients with pelvic failures are rarely successful [14]. Indeed, 1- and 2-years survival for patients developing a local recurrence after cystectomy is only 8 and 3% respectively, with a median survival of <4 months [15]. For patients with lymph node recurrence prognosis is somewhat better, but nevertheless still disappointing with reported 1- and 2 years survival of 42 and 11% respectively [15]. Moreover, pelvic recurrences are often debilitating with pain, lymphedema and venous thrombosis as known morbidities. If patients with local or lymph node recurrence are treated with external beam radiotherapy (EBRT), 1-year survival is significantly improved from 2% (no EBRT) to 27% [15]. Apparently, improving loco-regional control can impact survival in MIBC. We hypothesize that an earlier implementation of pelvic EBRT i.e. in the immediate postoperative (i.e. adjuvant) setting, will prevent local and pelvic nodal recurrence and improve disease free- and overall survival as loco-regional recurrence is linked to the development of distant metastasis [16, 17].

Little is known about the timing of EBRT combined with radical cystectomy in MIBC. Preoperative EBRT can prevent intra-operative seeding of tumor cells and sterilizes microscopic extensions in the perivesical tissues. However, a meta-analysis of six randomized trials showed no clear benefit for preoperative irradiation [18]. Adjuvant EBRT also has the advantage of dealing with microscopic cells along with a better identification of patients who are really at increased risk of developing local recurrence based on histological information of the primary tumor. Already two decennia ago, adjuvant EBRT was tested in a prospective randomized trial and resulted in a 20% increase in 5-year disease free survival (DFS) [19, 20]. These results were supported by a non-randomized controlled Radiation Therapy Oncology Group trial [21]. Also in the era of modern surgery it is suggested that adjuvant radiotherapy improves outcome. Shariat et al. found that, although a limited number of patients, adjuvant radiotherapy was independently associated with lower disease recurrence (HR: 3.3, 95% CI: 2.2–4.9; *p* < 0.001) and improved disease specific survival (HR: 2.4, 95% CI: 1.6–3.7; *p* < 0.001) while in the same study the impact of adjuvant chemotherapy on similar outcomes was less clear [6]. Despite those encouraging results, severe intestinal toxicity rates hampered the enthusiasm to use adjuvant EBRT, in fact till now [19, 21]. However, the technology that was used in the above-mentioned trials is outdated and conclusions concerning toxicity do not apply to the current technologies such as intensity-modulated radiotherapy (IMRT) and volumetric arc therapy (VMAT) and image guided radiotherapy [22–24]. Therefore, it is reasonable and even desirable to reconsider the use of adjuvant EBRT in properly selected MIBC patients.

This “proper” selection should be based on clinical, pathological, radiological and biological predictors for local and locoregional failure. Well-known clinical and pathological predictors are T-stage, lymph node status [6, 25], presence of lymphovascular invasion [6] and surgical margin status [10].

To select those MIBC patients who will benefit most from postoperative EBRT it is important to first rule out distant metastasis. So far, conventional imaging techniques fail to detect recurrences or metastasis from bladder cancer at an early stage. Although only few studies have evaluated the potential role of ^18^F–FDG-PET-CT in the loco-regional staging of patients with MIBC, specificity and negative predictive values mounts to >90% rendering it an interesting tool in the staging of MIBC patients, although its use is currently recommended only within clinical trials [26]. ^18^F–FDG-PET-CT has also been studied in the recurrent setting. Although the evidence is limited it has been suggested that a good diagnostic performance is obtained with ^18^F–FDG-PET-CT in the recurrent setting of MIBC [27]. By implementing ^18^F–FDG-PET-CT prior to the start of adjuvant radiotherapy we aim to exclude patients with distant metastasis as these patients are less likely to benefit from this treatment approach.

Additionally, circulating biomarkers can be used to identify patients who are at increased risk for local and pelvic nodal relapse for whom this multimodality therapy is presumed to be most beneficial. Biomarkers will be evaluated to determine if they can help in selecting those patients most likely to benefit from adjuvant radiotherapy.

## Methods/design

This study is approved by the Ethics committee of the Ghent University Hospital (EC2014/0630) and is registered on clinicaltrials.gov (NCT02397434). Patients with high risk (see below) of developing local or pelvic nodal recurrence after radical cystectomy with ePLND will be offered adjuvant EBRT within a multicentric prospective phase II trial.

### Objectives

*Primary endpoint*
○ Acute toxicity defined as toxicity occurring during or within 3 months following adjuvant EBRT and scored by:▪ Acute Radiation Therapy Oncology Group (RTOG) small and large intestine toxicity [28] and Common toxicity criteria version 4.0 (CTC v4.0) [29]▪ Acute RTOG [28] and CTC v4.0 [29] bladder toxicity for patients with a neobladder only

*Secondary endpoints*
○ Quality of life (QOL) scoring using the EORTC QLQ-C30 supplemented with QLQ-BLM30 prior to, at the end and 1 month after adjuvant EBRT, then 3-monthly during the first year and 6-monthly up to 2 years.○ Assessment of quality-adjusted-life-years with the EuroQol classification system (EQ-5D) [30]. A written consent to use this system was obtained from the EuroQol Group Foundation.○ Assessment of erectile function using the International Index of Erectile Function (IIEF) questionnaire [31] in males and sexual function in females [32].○ Assessment of voiding pattern using the International prostate Symptom Score (I-PSS) [33] and International Consultation on Incontinence Modular Questionnaire Urinary Incontinence (ICIQ-UI) Short Form [34] for patients with a neobladder.○ Late toxicity due to radiotherapy will be scored using RTOG [28] and CTC v4.0 [29] scoring systems. Late toxicity is defined as toxicity lasting more than 3 months after cessation of adjuvant EBRT, or starting more than 3 months after the end of adjuvant radiotherapy.○ Local control rate defined as absence of recurrence within the pelvis. This will be evaluated on pelvic CT scans performed on predefined time-points (see below) or in case of suspicion of recurrence.○ DFS defined as survival without evidence of disease recurrence (neither local recurrence, recurrence in lymph nodes or distant metastasis) and is calculated from date of radical cystectomy till diagnosis of local, regional or distant recurrence on CT scan at predefined time-points or in case of suspicion of recurrence.○ Bladder cancer specific survival calculated from date of radical cystectomy till death due to MIBC.○ Overall survival calculated from date of radical cystectomy till death of any cause.○ Serum samples and urine samples after cystectomy will be collected and stored in a biobank. Biomarkers will be evaluated on all samples in duplicate and correlated with DFS and bladder cancer specific survival.

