### Data analysis

The primary endpoint is acute toxicity defined as any toxicity from start of adjuvant EBRT up to 3 months following adjuvant EBRT.

The incidence of late toxicity will be recorded. Actuarial risk estimates for developing late toxicity will be calculated using Kaplan Meier analysis.

QOL will be evaluated pre-radiotherapy, at the end of radiotherapy and 1 month after radiotherapy. Thereafter a 3 monthly evaluation will be performed during the first year and 6-monthly up to 2 years after radiotherapy.

DFS, bladder cancer specific survival and overall survival will also be calculated using Kaplan Meier actuarial analysis. Survival times are defined from the date of radical cystectomy until an event or last follow up.

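### The DFS calculation rule stops only at recurrence on CT and omits death, in conflict with the endpoint's name and opening clause; applied literally, it would overstate DFS

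*Protocol article*

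**What the plan says.** The protocol article lists DFS among the secondary endpoints in Objectives. The sentence has two parts. The first gives the concept: "DFS defined as survival without evidence of disease recurrence (neither local recurrence, recurrence in lymph nodes or distant metastasis". The second gives the calculation: it "is calculated from date of radical cystectomy till diagnosis of local, regional or distant recurrence on CT scan", with the CT done either at a scheduled time or when recurrence is suspected.

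The next two endpoints in the same list each name death. One is "Bladder cancer specific survival calculated from date of radical cystectomy till death due to MIBC". The other is "Overall survival calculated from date of radical cystectomy till death of any cause".

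The Data analysis section gives the estimator, "DFS, bladder cancer specific survival and overall survival will also be calculated using Kaplan Meier actuarial analysis", and the time rule, "Survival times are defined from the date of radical cystectomy until an event or last follow up". It does not restate what a DFS event is, and it names no competing-risk method.

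DFS has a second use in Objectives: "Biomarkers will be evaluated on all samples in duplicate and correlated with DFS and bladder cancer specific survival".

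**The concern.** The two halves of the DFS sentence do not agree. A patient who has died is not surviving free of disease, so the opening clause and the name imply that death ends DFS. The calculation rule ends it only at a recurrence diagnosed on CT. A programmer would work from the calculation rule, and under that rule a patient who dies without documented recurrence has no event. The only other stopping point that Data analysis offers is last follow-up, which means censoring.

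Such deaths are plausible in this trial:

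- **Unrelated deaths.** Background says that bladder cancer incidence rises with age. The inclusion criteria set no upper age limit and admit WHO performance state up to 2.
- **Fatal complications.** Background and Discussion both say that severe toxicity held back earlier adjuvant radiotherapy. A fatal complication before recurrence would not count against DFS.
- **Bladder cancer deaths without a confirming scan.** Background cites a median survival below 4 months after local recurrence. Follow up schedules CT in asymptomatic patients every 3–6 months in year one and every 6 months up to year five. A patient could recur and die between scans. That death would count for bladder cancer specific survival but be censored for DFS.

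At stake are the level of the reported DFS curve, its comparability with any published DFS that counts deaths, and the meaning of the biomarker correlation, which would be with time to recurrence and not with DFS. A DFS curve that counts all deaths cannot lie above overall survival; a curve built on the written rule can.

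**Working it through.** **1. The plan's own figure.** No figure is stated for DFS. The only design figure is the sample size of 76, from the Sample size section: 95% confidence, expected severe toxicity 25%, half-width 10 points, 5% missing data.

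n = 1.96² × 0.25 × 0.75 / 0.10² = 72.03, and 72.03 / 0.95 = 75.8, which rounds up to 76.

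The figure reproduces. It rests on toxicity alone, so the DFS definition cannot change it.

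**2. What each rule estimates.** Let h_r be the yearly hazard of recurrence and h_d the yearly hazard of death without documented recurrence, both taken as constant.

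- Rule as written, recurrence-free deaths censored: Kaplan-Meier tends to exp(−h_r·t).
- Death counted as an event: DFS(t) = exp(−(h_r + h_d)·t).
- Overstatement = exp(−h_r·t) × [1 − exp(−h_d·t)].

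The overstatement is never negative, and it is zero only when h_d = 0.

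**3. Numbers at t = 5 years.** The documents give neither hazard. The ranges 0.15–0.30 for h_r and 0.02–0.06 for h_d are assumptions.

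| h_r | h_d | As written | Death counted | Overstatement |
|---|---|---|---|---|
| 0.30 | 0.02 | exp(−1.50) = 0.223 | exp(−1.60) = 0.202 | 2.1 points |
| 0.25 | 0.04 | exp(−1.25) = 0.287 | exp(−1.45) = 0.235 (0.2346) | 5.2 points |
| 0.15 | 0.04 | exp(−0.75) = 0.472 | exp(−0.95) = 0.387 | 8.6 points |
| 0.15 | 0.06 | exp(−0.75) = 0.472 | exp(−1.05) = 0.350 | 12.2 points |

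The first and last rows are the smallest and largest gaps in the assumed range.

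**4. A second set of assumptions.** Fix a horizon at which net recurrence is 50%, so the rule as written reads 50.0%. With net recurrence-free death of 2%, 5%, 10% and 15% at that horizon, DFS with death counted is 49.0%, 47.5%, 45.0% and 42.5%, a gap of 1.0 to 7.5 points. Letting net recurrence run from 40% to 60% widens this to 0.8 to 9.0 points. These gaps are smaller than in step 3 because less death is assumed: 0.02–0.06 per year over five years is a net probability of 1 − exp(−0.10) = 9.5% to 1 − exp(−0.30) = 25.9%.

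A Kaplan-Meier simulation with 76 patients and 4,000 runs, at 50% net recurrence and 10% net death, gave mean estimates of 50.0% with deaths censored and 44.9% with deaths counted. The formula gives 50.0% and 45.0%.

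**5. Why a new name alone is not enough.** Suppose the written rule is kept as a recurrence endpoint. At h_r = 0.15 and h_d = 0.04, one minus Kaplan-Meier gives 1 − 0.472 = 0.528 recurred by 5 years. The cumulative incidence with death as a competing event is (0.15 / 0.19) × (1 − 0.387) = 0.484. Censoring deaths therefore overstates the share of patients who actually recur.

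**The case against.** The strongest reply is that the opening clause already makes death count, since it speaks of survival, and that the rest of the sentence only says how recurrence is dated. Censoring at death is nowhere stated. It follows from reading Objectives and Data analysis together, and a full protocol or analysis plan that is not shown may settle it. This stands in part: the documents do not show that the investigators intend to censor deaths. It does not remove the problem, because the calculation rule is stated here and conflicts with its own opening clause.

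Other points that stand:

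- Deaths do not vanish from the trial. All enter overall survival, and those due to bladder cancer also enter bladder cancer specific survival.
- CT on suspicion of recurrence narrows the route by which a recurrence goes undocumented, though it does not close it.
- DFS is one of several secondary endpoints in a single-arm trial. Discussion gives the aim as supporting the hypothesis that toxicity is acceptable.

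A reader might infer more than the documents support. One such reading is that the whole efficacy hypothesis rests on DFS. Background names local and nodal recurrence, DFS and overall survival together, and the biomarkers are also correlated with bladder cancer specific survival. Another is to weigh the bias against the 20% increase in 5-year DFS that Background cites from a randomized trial. That is a between-arm difference, that trial's DFS definition is not shown, and no formal comparison with it is planned. It is no yardstick for the level of a single-arm curve.

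The upper end of the size range is also open to challenge. The 12-point case implies a 5-year DFS of 35%, and DFS counting all deaths cannot exceed overall survival, which Background puts as low as 22% for pT3 or higher. Holding DFS at or below 22% within the assumed hazards leaves gaps of about 2 to 8 points. For the upper figure, h_d = 0.06 requires h_r of about 0.243, and exp(−1.214) − 0.220 = 0.077. However, 22% is the lowest series cited, and eligibility is not confined to pT3 or higher, so this narrows the likely range without fixing it.

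**Conclusion.** The point holds as an internal conflict with a predictable direction of error. The DFS calculation rule omits death, while the endpoint's name and opening clause imply it. If that rule is followed under the stated Kaplan-Meier plan, recurrence-free deaths are censored, and the curve shows freedom from recurrence and sits above DFS.

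The 5-year overstatement is about 2 to 12 points under the assumed hazards, and 0.8 to 9.0 points under the second set of assumptions. Both ranges depend on a rate of recurrence-free death that the documents do not give. Only the direction is certain.

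The documents do not support saying that DFS will certainly be biased, that toxic deaths go unreported, or that the trial's main conclusion is at risk. The primary endpoint and the 76 patients are untouched. This should be fixed before DFS is analysed, as a matter for a secondary endpoint and its biomarker correlation.

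**What to change.** Replace the calculation clause so that DFS runs from radical cystectomy to the first of local, nodal or distant recurrence or death from any cause. Censor only patients who are alive and recurrence-free at last follow-up. State the same event in Data analysis, and use it for the biomarker correlation.

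If the investigators want to keep the present rule, call it time to recurrence, report it as cumulative incidence with death without recurrence as a competing event, and do not label it DFS.

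The cost is about one sentence in each section. Deaths and their dates are already needed for overall survival, so there is no new data collection and no change to the sample size.
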